### Study endpoints

The primary endpoint is the reduction in performance on cognitive tests defined as follows: After exclusion of local recurrence, decreased detailed neuropsychological assessment score compared to the patient's baseline score before radiotherapy for at least 2 cognitive domains.

Secondary endpoints are:Differences in biomarkers’ concentration between the measurements before RT and: at the end of the RT, RT + 4 weeks, RT + 12 months and RT + 36 months.Changes in MRI images compared to the baseline imaging.Correlations between dosimetry, cognitive decay and MRI abnormalities onset after RT.

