**Fig. 1 Fig1:**
[figure not shown]
Study procedure

Every 3 months, once the MRI of the patient is done, a medical visit occurs during which a short cognitive assessment is performed (the CSCT).

Cognitive tests, scales and questionnaires used for the formal assessment are listed in Table 2. An extensive evaluation lasting 2 h is performed with a trained neuropsychologist, followed by self-reported and caregiver-reported scales and questionnaires. The explored domains are intellectual efficiency, general functioning, verbal and visual episodic memory, attention, executive functioning, language, visuospatial and visuoconstructive abilities, mood, fatigue, quality-of-live, subjective complaints and autonomy. The formal assessment occurs at baseline and yearly after radiotherapy. In case of CSCT score decrement during follow-up the next yearly formal assessment is performed earlier. CSCT decrement is defined as a loss of 1 standard deviation compared to baseline (given its low learning-effect and good stability in controls [22]), during two consecutive assessments. The necessity of detecting a decrement during two visits permits to insure that a variation in score is not due to a transitory cause like an infection or fatigue, which is reversible and not linked to leukoencephalopathy. This procedure will allow to study the nature, course and incidence of cognitive decrement following radiotherapy in this population. At baseline and during the follow-up, the CSCT will be compared to the formal cognitive assessment to study its sensibility to detect impairments in this context.

**Table 2 Tab2:** Tests and questionnaires used for the cognitive, mood and behavioral assessment

Domain	Tests, scales and questionnaires
Cognitive assessment	
Intellectual efficiency	National Adult Reading Test (French version) [38]
General functioning	Mini Mental State Examination [39]
	Montreal Cognitive Assessment [40]
	Dementia Rating Scale-2 [41]
Verbal episodic memory	RLRI-16 (Adaptation of the Grober-Buschke test) [42]
Visual episodic memory	Rey-Osterrieth Complex Figure [43]
Executive functions and Attention	Digit Span forward [44]
	Digit Span backward [44]
	Letter-number sequencing [44]
	Categorical and phonetic word fluency [45, 46]
	Trail Making Test [45, 46]
	Computerized Speed Cognitive Test [22]
	Stroop color-word Test [45, 46]
Langage	Boston Naming Test [47]
	Token Test [48]
Visuospatial and visuoconstructive functions	Rey-Osterrieth Complex Figure [43]

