#### Analysis of evaluation criteria

Based on primary endpoint definition, the estimate of the incidence of cognitive impairment related to radio-induced leukoencephalopathy in our cohort will be made.

An analysis of the dose–response relationship between radiation dose absorbed by different brain structures and cognitive abnormalities observed after radiotherapy will be made using a multivariate Cox model taking into account the delivered dose to the organ of interest and the time occurrence of cognitive complications. An adjustment on risk factors for cognitive complications will be achieved. Similarly for patients with cognitive impairment before radiotherapy, an analysis of potential associated risk factors will be carried out with the use of a multivariate model.

Secondary judgments criteria, including changes in MRI images relative to the reference imaging and changes in series of biological markers between measurements before RT, 4 weeks, 12 month and 36 months after RT, will be analyzed by parametric distribution comparison tests (Z) or nonparametric if needed (Wilcoxon tests).

In addition, an analysis will be conducted of the sensitivity and specificity of the CSCT to demonstrate cognitive impairment by comparing the CSCT performed before radiotherapy and detailed neuropsychological assessment (gold standard) achieved at the same time. More, CSCT decay during follow-up will be analyzed by comparing its results to formal assessment during years after treatment, to study its sensibility in detecting cognitive decrement after radiotherapy.

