### Time plan

Initial inclusion data collection began in April 2015 and will continue through 2017. First statistical analysis about cognitive impairment related to radio-induced leukoencephalopathy incidence will be available in the end of 2016.

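### CSCT-triggered early formal assessments make detection of the primary event depend on the CSCT, which affects the Cox event times, follow-up CSCT sensitivity and the end-2016 incidence estimate

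*Protocol article*

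**What the plan says.** Under Study endpoints, the primary event is, once local recurrence has been excluded, a "decreased detailed neuropsychological assessment score compared to the patient's baseline score before radiotherapy for at least 2 cognitive domains". It can therefore be recorded only when the detailed battery is given.

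Under Procedures, "The formal assessment occurs at baseline and yearly after radiotherapy". The CSCT is given at 3-monthly visits, and "In case of CSCT score decrement during follow-up the next yearly formal assessment is performed earlier". The trigger is strict: "CSCT decrement is defined as a loss of 1 standard deviation compared to baseline", and the loss must be seen at two consecutive visits.

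Three stated analyses use the results of these assessments:

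- Analysis of evaluation criteria plans a dose-response analysis "using a multivariate Cox model taking into account the delivered dose to the organ of interest and the time occurrence of cognitive complications".
- The same section assesses the CSCT against the formal battery twice: before radiotherapy, with both tests done together, and again during follow-up.
- Time plan announces: "First statistical analysis about cognitive impairment related to radio-induced leukoencephalopathy incidence will be available in the end of 2016". Inclusion began in April 2015.

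The article nowhere separates triggered from scheduled assessments in these analyses.

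**The concern.** The CSCT decides, in part, when the outcome is looked for. A patient whose CSCT falls is tested early. A patient with the same impairment but a stable CSCT is tested at the yearly date, and only if still alive and free of local recurrence.

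Three results are at stake. The recorded time of impairment mixes the disease process with the testing process. The CSCT is judged in follow-up on a sample in which CSCT-positive patients are more likely to be verified. And a first incidence figure taken before most patients reach their first yearly assessment draws its early cases from patients selected by a falling CSCT. Incidence of cognitive impairment is the main objective, so the third matters most.

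**Working it through.** **Plan's own figure.** The sample size range is not in dispute and reproduces. With n = z²P(1−P)/d² and z = 1.96, a half-width of d = 0.05 (not stated; inferred because it returns both figures) gives 245.9 for P = 0.2 (stated 246) and 384.1 for P = 0.5 (stated 384).

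**Inputs from the article.** 400 patients; recruitment for 2 years; start April 2015; formal assessment yearly; CSCT every 3 months; median survival below 18 months.

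**Assumptions.** Uniform accrual; 2-3 months from inclusion to end of radiotherapy; 3-monthly visits counted from the end of radiotherapy, so the earliest confirmed CSCT fall is about month 6 (Fig. 1 is not available to check this); exponential survival with median 18 months, independent of impairment.

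**Calendar at the end of 2016 (21 months after start).**

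- Enrolled: 400 × 21/24 = 350.
- Could have reached 12 months after radiotherapy, ignoring deaths: 400 × (21 − 12 − 2)/24 = 117, or 400 × (21 − 12 − 3)/24 = 100.
- Between 6 and 12 months: 400 × 6/24 = 100. These have a post-radiotherapy formal assessment only if triggered.
- Under 6 months: 350 − 117 − 100 = 133, or 350 − 100 − 100 = 150. These cannot yet have been triggered.
- Survival to month 12: 0.5^(12/18) = 0.63, so about 63-74 of the 100-117 would be alive at their yearly assessment.

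**Simulation.** 40,000 patients per setting, 12-month risk of impairment 0.30, median survival 18 months. The CSCT responds to a true event with probability 0.4 to 0.8. False triggers are 0 in the detection runs, 2% per visit in the Cox and sensitivity runs, and 0 or 2% in the end-2016 runs. A triggered assessment replaces that year's scheduled one. Local recurrence is not modelled.

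*Detection.* Without a trigger, 78% of true events are detected before death or month 36, at a mean delay of 6.4 months. With it, 81-84% are detected, at a mean delay of 5.3 to 4.4 months.

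*Cox hazard ratio, detection date as event time.*

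| CSCT response, low / high dose | True 1.00 | True 1.50 |
|---|---|---|
| No trigger | 1.00 | 1.50 |
| 0.6 / 0.6 | 1.01 | 1.51 |
| 0.4 / 0.8 | 1.09 | 1.64 |
| 0.8 / 0.4 | 0.93 | 1.38 |

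*Follow-up CSCT sensitivity.*

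| CSCT response | All true events | Verified, no trigger | Verified, with trigger |
|---|---|---|---|
| 0.4 | 0.341 | 0.378 | 0.401 |
| 0.6 | 0.466 | 0.518 | 0.545 |
| 0.8 | 0.593 | 0.661 | 0.687 |

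The trigger adds 2.3 to 2.7 points. Events never verified, mainly because of death, add 3.7 to 6.8. With the trigger, all CSCT-positive but only 52-56% of CSCT-negative patients get a formal assessment.

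*End-2016 incidence (lag 1.5 months in this run, 350 enrolled).*

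| Denominator | No trigger | With trigger |
|---|---|---|
| Assessed patients | 0.30 | 0.34 to 0.39 |
| All enrolled | 0.067 | 0.082 to 0.098 |

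The low figure over all enrolled comes from short follow-up and death. The trigger raises it slightly.

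**The case against.** The strongest reply has four parts.

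**The Cox model.** The article does not say that the assessment date is the event time, and interval censoring is the kind of detail left to an analysis plan that is not shown. That is fair. But the design observes no other date, and the unequal spacing of assessments is fixed by the visit rule whatever that plan says. A reader might infer that the rule makes dose or risk factors appear to bring impairment forward. The documents do not support that. With equal CSCT response the hazard ratio is essentially unbiased, nothing shows that response differs by dose, and if it did the direction could be either. A difference is only plausible: the CSCT measures processing speed, while the dose analysis covers structures such as the hippocampus.

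**CSCT accuracy.** A reader might infer that all the accuracy results are compromised. The baseline comparison is not, since both tests are done together. In follow-up, CSCT-negative survivors are still assessed yearly. A simple sum that verifies every CSCT-positive case at month 6 and every CSCT-negative case at month 12 turns a true 60% into 0.6 × 0.794/(0.6 × 0.794 + 0.4 × 0.630) = 65%, but this overstates the trigger's own share, which is 2-3 points.

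**End of 2016.** A reader might infer an inflated incidence figure. The article fixes neither the denominator nor the estimator. Over assessed patients the figure is too high, and over all enrolled it is too low. What stands is that neither simple denominator estimates the 12-month risk.

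**The rule helps detection.** It does: more events are found, and sooner. That is a reason to keep the rule and adapt the analysis.

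**Conclusion.** The point holds in limited form. As written, the plan makes ascertainment of the primary event depend on the CSCT, and three stated analyses inherit this to different degrees.

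- The end-2016 incidence is the most affected: 34-39% among assessed patients, or 8-10% over all enrolled, against an assumed 30%.
- Follow-up CSCT sensitivity is overstated by about 6 to 9 points in total, of which 2-3 are due to the trigger.
- The Cox hazard ratio is at risk only if CSCT response varies with dose or a risk factor. Even a response of 0.4 against 0.8 moved it by less than 10%.

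The calendar count rests on the 2-year recruitment in the article and an assumed 2-3 month lag. The other sizes rest on assumed risk, survival and CSCT response. The directions for follow-up sensitivity and for end-2016 incidence were the same across all values tried.

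**What to change.** Keep the visit rule and change the analysis.

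1. For the dose-response analysis, use an interval-censored proportional hazards model on the actual formal assessment dates, from last negative to first positive. Handle death before assessment and local recurrence explicitly, for example as competing events in an illness-death model. Moving triggered results onto a fixed yearly grid is not enough, because an early negative test would then count as event-free to month 12.

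2. For follow-up CSCT sensitivity and specificity, report triggered and scheduled assessments separately. Weight by the inverse probability of verification, modelled on CSCT history, survival and recurrence status. A correction that uses the CSCT alone would miss patients lost to death or recurrence. State the assumption that verification depends only on recorded data.

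3. Restrict the end-2016 incidence estimate to patients whose inclusion date allows 12 months after radiotherapy, with earlier deaths and recurrences handled as in item 1, or postpone it. Restriction alone leaves a small excess, because triggered cases who die before month 12 are counted while untriggered ones are not. With 12-month risk 0.30 and CSCT response s, the probability of being triggered at month 6 or 9 and dying before month 12 is s × [0.0853 × (0.794 − 0.630) + 0.0780 × (0.707 − 0.630)] = 0.020s. The risk among assessed patients is then (0.189 + 0.020s)/(0.630 + 0.020s), which is 0.31 for s = 0.4 and 0.32 for s = 0.8.

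The cost is a somewhat more complex analysis and a first estimate that rests on fewer patients or comes later. No extra assessments are needed.

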**Method/Design:**

The EpiBrainRad study is a prospective cohort study including newly diagnosed high grade gliomas patients treated by radiotherapy and concomitant-adjuvant temozolomide chemotherapy. Patients are included between their surgery and first day of radio-chemotherapy, and the follow-up lasts for 3 years after treatment. Cognitive functioning assessments, specific blood biomarkers measures and magnetic resonance imagery are performed at different moment during the follow-up, and a specific dosimetric assessment of organs involved in the beam fields is performed. Firstly, leukoencephalopathy incidence rate will be estimated in this population. Secondly, correlations between cognitive impairments and dosimetry, biomarkers ranges and anomalies on imagery will be analyzed in order to better understand the onset and evolution of cognitive decrement associated with radiotherapy. Furthermore, a new cognitive test, quickly and easily performed, will be studied to determine its sensibility to detect leukoencephalopathy decrement.

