From a biological point of view, biological mechanisms of the initiation and progression of cognitive impairements is not well known. However, specific biomarkers predictive of the cognitive impairments in this population would help in screening patients at risk of neurotoxicity. Currently, biomarkers of neurotoxicity have been poorly studied. Thus, several markers deserve to be explored such as the S-100B protein known to be a marker of traumatic cerebral lesion, neurodegenerative diseases and aggressive gliomas [17], specific isoprostanes (as 8,12-*iso*-iPF_2α_-VI) implicated in the oxidative/nitrate stress in neurodegenerative diseases [18] and homocystein which plasma concentration has been associated with poor memory performances in old individuals [19]. Furthermore, new biomarkers seems to be potentially very interesting. Indeed, micro RNA and microparticules have been identified as potential biomarkers of neurological defects [20, 21]. Then the strategy proposed is to test classical and new biomarkers in order to individualize those, which could be accurate for the screening of patients at risk of cognitive impairments.

At last, assessment of cognitive impairment is difficult because the exploration of cognitive side effects is not systematic and often depends on patients’ complaints and clinicians’ sensibility to this aspect. A formal neuropsychological assessment can’t be performed in routine, as often as it should be for an adapted follow-up of brain tumor patients. Indeed, it is time consuming, needs expert professionals and validated material, and consequently it is not easily implemented in most medical center. A new tool for exploration of cognitive deficits is the *Computerized Speed Cognitive Test* (Legal deposit: IDDN.FR.001.180018.000.S.P.2014.000.31230) (CSCT) [22]. The CSCT was first developed to assess information speed processing in multiple sclerosis. Because it presents a low learning-effect and focuses on a cognitive characteristic often impaired in neuro-oncologic population, it could be used to detect a cognitive deterioration during repeated medical visits, and thus be used as an alarm to start a more extensive formal assessment. Then, it is suitable for the follow-up of a cohort of patients treated for brain tumor and allows to give quick and reliable information on cognitive impairment, compatible with the usual clinical follow-up of the patients.

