### Procedures

Figure 1 gives an overview of the study flowchart. Patients’ inclusion occurs after surgery and before radio/chemotherapy (Baseline). At this time, individual information including demographic information, medical background and tumor characteristic are collected.

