Self-reported Scales	
Mood	Anxiety questionnaire of Goldberg [49]
	Center for Epidemiologic Study Depression Scale [50]
Fatigue	FACIT Fatigue Scale [51]
Memory complaint	MacNair and Khan questionnaire [52, 53]
Quality-of-life	EORTC QLQ-C30 [54]
	EORTC QLQ-BN20 [55]
Care-giver-reported Scales	
Dysexecutive syndrome	ISDC [45, 46]
Autonomy	EIADL [56]

Baseline and trimensual MRI during the medical follow-up are used for extra analysis in order to study white matter abnormalities and cortical atrophy. Moreover, tumor response or progression will be assessed by the Response Assessment in Radio-Oncology working group (RANO) Criteria [25]. The white matter lesion quantification will follow the procedure described by Wahlund et al. [26] using a 4 points scale (0: no lesion; 1: focal lesions; 2: beginning confluence of lesion; 3: diffuse involvement of the entire region). The cortical atrophy quantification will follow the procedure described by Pasquier et al. [27] using a 4 points scale (0: absence of atrophy; 1: mild atrophy; 2: moderate atrophy; 3: severe atrophy). White matter lesion and cortical atrophy is assessed for all key region listed in Table 3. A double blind lecture of the MRI will be done in order to quantify these anomalies. Radiological outcomes will then be correlated with cognitive outcomes.

**Table 3 Tab3:** Regions prospectively explored on MRI and dosimetric analysis

Key regions investigated		
	MRI	Dosimetry
Frontal lobes	*	*
Temporal lobes	*	*
Parietal lobes	*	
Occipital lobes	*	
Cerebellum	*	*
Basal ganglia	*	
Brain Stem	*	*
Hippocampus		*
Corpus Callosum		*
Periventricular white matter		*

* anatomical region investigated

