The need for a biological marker of cognitive disorders has proven to be urgent, both for diagnosis and for monitoring of the diseases. Among the advantages that such markers may bring, we emphasize the possibility of early and even preclinical diagnosis of the disease with the subsequent correct treatment of disease by the medical team. Biomarkers for cognitive impairment have been an issue in recent years. The value of a variety of these markers, like amyloid beta or tau, has been evaluated and discussed [28]. Besides proteins, microRNAs have also demonstrated their potential as non-invasive biomarkers from blood and serum for a wide variety of human pathologies [29]. A deregulation of microRNA expression might be involved in neurological dysfunction or neurodegenerative processes. A recent serum profiling of Alzheimer disease patients provided evidence that expression changes of circulating miRNAs may be valuable biomarkers for this neurological disease [20]. In addition, microparticles have been implicated to have pathological roles in many diseases such as Alzheimer’s disease. The consensus among recent studies is that increased levels of specific types of microparticles in plasma may represent reliable biological markers for the onset and progression of central nervous system diseases [30].

Consequently, plasmatic classical biomarkers as S-100B protein, isoprostane 8,12-*iso*-iPF_2α_-VI, homocysteine and new ones, as micro RNA and microparticules (see Table 4) will be sampled in blood at baseline, 4 weeks, 12 months and 36 months after the end of radiotherapy. These biomarkers could be potential blood predictors of cognitive impairments [17, 19–21] and thus their concentration evolution after radiations will be analyzed. Additional blood sample tubes are stored to constitute a biological collection for future investigations about others biomarkers.

**Table 4 Tab4:** Biomarkers sampled in blood

Classical biomarkers correlated with cognitive impairments	S-100B protein [GenBank : NP_006263]
	8,12-iso-iPF2a-VI isoprostane
	Homocysteine [GenBank : NP_060084]
	microRNAs
New biomarkers	brain-miR-112 [GenBank : AF480510]
	brain-miR-161 [GenBank : AJ535829]
	hsa-let-7d-3p [GenBank : LM380164]
	hsa-miR-5010-3p [GenBank : LM38284]
	hsa-miR-26a-5p [GenBank : LM378769]
	hsamiR-1285-5p [GenBank : LM383022]
	hsa-miR-151a-3p [GenBank : LM379262]
	hsamiR-103a-3p [GenBank : LM378788]
	hsa-miR-107 [GenBank : LM378791]
	hsa-miR-532-5p [GenBank : LM379811]

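### The unadjusted whole-cohort before-after test of S-100B can hide or mimic a radiation-related change, because later values may carry tumour progression and the post-surgery baseline may carry surgery

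*Protocol article*

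**What the plan says.** All references are to the protocol article.

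- **Reference sample.** Under Procedures, patients' "inclusion occurs after surgery and before radio/chemotherapy (Baseline"). The abstract agrees: "Patients are included between their surgery and first day of radio-chemotherapy". The text shown states no minimum or common interval from surgery to the blood draw.
- **Sampling times.** Under Procedures, the markers "will be sampled in blood at baseline, 4 weeks, 12 months and 36 months after the end of radiotherapy".
- **Endpoint.** Study endpoints defines the biomarker outcome as the difference in "concentration between the measurements before RT and: at the end of the RT, RT + 4 weeks, RT + 12 months and RT + 36 months". The sampling list under Procedures has no end-of-radiotherapy draw; that is a separate discrepancy to reconcile and plays no part here.
- **Test.** Under Analysis of evaluation criteria, MRI and biomarker changes "will be analyzed by parametric distribution comparison tests (Z) or nonparametric if needed (Wilcoxon tests"). No covariate or tumour-status condition is attached.
- **What S-100B marks.** Background calls it "S-100B protein known to be a marker of traumatic cerebral lesion, neurodegenerative diseases and aggressive gliomas".
- **Tumour status.** The primary cognitive endpoint applies "After exclusion of local recurrence, decreased detailed neuropsychological assessment score". The biomarker endpoint in the same section has no such condition, although "tumor response or progression will be assessed by the Response Assessment in Radio-Oncology working group (RANO) Criteria".

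**The concern.** A before-after test in a cohort where every patient is irradiated attributes the whole mean change to whatever happened between the two samples. On the protocol's own description of S-100B, two things besides radiation can move it. Brain surgery precedes the reference sample, and the tumour may progress before the later ones. Any surgical contribution at baseline pushes the observed change down. Progression at 12 or 36 months can push it up.

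The tumour side matters in this population because the Discussion puts median survival below 18 months, so progression during follow-up will be common. The same Discussion accepts that progression can obscure the cognitive defect, and the cognitive endpoint is protected accordingly; the biomarker comparison is not.

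At stake is a secondary aim: choosing blood markers of neurotoxicity. S-100B could be dropped although it responds to radiation, or kept because it tracks tumour or surgical recovery.

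**Working it through.** **No figure in the protocol bears on this point.** The one calculated figure, the sample size range of 246 to 384, concerns the incidence proportion. What follows is a structural argument with labelled illustrations.

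**Structure.** Write the expected change in S-100B at a later draw as

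E(change) = δ + q·t − b,

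where δ is the radiation-related change, q the share of sampled patients with progression, t the mean rise in those patients, and b any surgical elevation still present at baseline. The planned test sees only the sum. The documents give none of q, t, b or δ.

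**Illustration 1: ratio scale.** Assume a true radiation-related ratio of 1.20 and a baseline raised by a fraction e. Observed ratio = 1.20/(1 + e).

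| e | Observed ratio |
|---|---|
| 0.10 | 1.20/1.10 = 1.09 |
| 0.30 | 1.20/1.30 = 0.92 |
| 0.50 | 1.20/1.50 = 0.80 |

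The direction reverses once e exceeds 0.20.

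**Illustration 2: the planned test.** Assumptions:

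- Paired two-sided normal test at 5% (Planned analysis gives two-sided 5%).
- Within-patient correlation ρ, so the SD of change is √(2(1 − ρ)) baseline SDs.
- Exponential survival with an 18-month median. Of the 400 planned patients, 400·exp(−ln 2·12/18) = 252 would be alive at 12 months and 400·exp(−ln 2·36/18) = 100 at 36 months. The protocol says the median is below 18 months, so these counts err on the high side. I use N = 250 and N = 100.

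With N = 250 and ρ = 0.5, the SD of change is 1 and the SE is 1/√250 = 0.063.

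*Mimicking (no radiation effect, net non-radiation shift of the size shown):*

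| Shift (SD) | N = 250, ρ = 0.5 | N = 250, ρ = 0.3 to 0.7 | N = 100, ρ = 0.5 |
|---|---|---|---|
| 0.1 | 35% reject | 27% to 53% | 17% |
| 0.2 | 88.5% reject | 76% to 98% | 52% |

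The test is two-sided, so these rates apply whether the shift is a fall from a surgical baseline or a rise from progression.

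*Masking (true rise 0.2 SD, N = 250, ρ = 0.5):*

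| b (SD) | Net change (SD) | Significant rise | Significant fall |
|---|---|---|---|
| 0 | +0.2 | 88.5% | 0% |
| 0.1 | +0.1 | 35% | 0% |
| 0.2 | 0 | 2.5% | 2.5% |
| 0.4 | −0.2 | 0% | 88.5% |

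These results show how sensitive the test is to small shifts. They do not show that such shifts exist.

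**The case against.** **The article announces more than this test.** Objectives speaks of correlating biological abnormalities with cognitive impairment, and Planned analysis announces that biomarker changes will be examined according to the dose absorbed in different brain areas. A dose-related analysis within the cohort is much less exposed to a post-surgical fall that all patients share. This stands. A reader might infer that the study cannot tell whether S-100B changed because of radiation; the documents do not support that. The point concerns the before-after test taken alone.

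**The surgical mechanism is not shown.** The window in the abstract and Procedures is for inclusion. Nothing says that blood is drawn at an arbitrary moment within it, and the study-procedure figure is not available here. The interval from surgery and the marker's clearance are not given. This stands too: the text supports saying that the baseline may reflect surgery, not that it does.

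**Only S-100B is described this way.** The isoprostane, homocysteine, microRNAs and microparticles carry no stated sensitivity to brain trauma or glioma. It is tempting to extend the criticism to all biomarkers, but the text does not support that.

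**Covariates for a secondary endpoint may sit in the full protocol or analysis plan.** This is fair for detail. But the article does name the test, and it conditions the cognitive endpoint on recurrence while leaving the marker endpoint unconditioned. Following it as written mixes tumour signal into the later S-100B changes.

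**RANO status arises after treatment.** Entering it as an ordinary covariate could itself distort a radiation effect. This is accepted, and the fix reports a separate comparison instead.

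**Conclusion.** The point holds for S-100B and for the unadjusted before-after comparison. By the protocol's own account the marker responds to brain trauma and aggressive glioma, the reference sample follows surgery, and the later samples are not conditioned on tumour status although that status is collected. The test alone can therefore hide or mimic a radiation-related change. The tumour component is the firmer of the two, since the protocol already guards its cognitive endpoint against it; the surgical component is possible but not demonstrated.

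The size cannot be derived from the documents. Under the assumed inputs above, a net shift of 0.1 to 0.2 SD at N = 250 is enough to produce a significant result in 35% to 88.5% of studies with no radiation effect, or to cut the chance of detecting a true 0.2 SD rise from 88.5% to 35% or less. The primary incidence estimate is not touched.

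**What to change.** Under Analysis of evaluation criteria:

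1. Alongside the whole-cohort result, report S-100B change separately for patients without progression by RANO at the sampling date, mirroring the exclusion of local recurrence in the primary endpoint. Do the same for the other markers for consistency.
2. State the analysis relating marker change to absorbed dose that Planned analysis announces, so that interpretation does not rest on the before-after test.
3. Include days from surgery to the baseline sample as a baseline covariate, or as a sensitivity analysis.
4. Keep the pre-radiotherapy sample as the main reference. Change from the sample 4 weeks after radiotherapy is at most supplementary, because that sample is already post-exposure and cannot show the initial effect.

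**Cost.** No added visits or samples, and RANO assessment is already planned. The surgery date must be taken from the clinical record, since the article does not list it among the data collected. The progression-free comparison will have fewer patients, especially at 36 months. They are a selected group, so it should be read beside the whole-cohort result and not in its place.
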